### Procedures

All eligible women will be approached at the time of booking into the clinic for caesarean section at around 36 weeks and will be given information about the study. Those women who meet the inclusion criteria and sign the informed consent form will be randomised to either the intervention or the control group by the independent researcher as explained previously (Fig. 1). On the day of the caesarean section, the sealed envelope containing instructions for the type of treatment will be picked up by the surgeon. The surgeon opens the envelope when the woman is ready for the caesarean section.

The control group will receive surgical excision of the keloid scar at the beginning of the procedure during skin incision. The baby will be delivered as normal, and routine wound closure will be performed in accordance with National Institute for Health and Care Excellence (NICE) guidelines as follows: The uterus is closed in two layers followed by closure of the rectus sheath, all using continuous sutures with 1-Vicryl (Johnson & Johnson). The fat layer is closed with interrupted plain gut sutures 2 cm apart. The skin layer is then closed with 3-0 Monocryl (Ethicon) in a sub-cuticular fashion.

The intervention group will receive surgical excision of the keloid scar after the delivery of the baby. Closure of the uterus layers, rectus sheath and the fat layer are completed as explained above. Then, triamcinolone acetone will be injected sub-dermally at the time of wound closure. Two ampules of triamcinolone acetonide (Kenacort®-A 10 suspension, Aspen Pharma Pty Ltd) will be administered at a single dose; each ampule contains 10 mg/1 ml active medication. The surgeon will inject one ampule along the entire length of the upper edge of the skin incision and one ampule along the entire length of the lower edge of the skin incision, using a 25 G needle.

After the procedure is completed, the surgeon will fill in the post-operation survey. The excision of the scar and administration of the injection will be performed by the surgeon who is scheduled to perform the surgery on that day. All the surgeons in the Department of Women’s and Newborn Health will be trained on how to perform the excision and injection of the triamcinolone. The Principal Investigator of the study will assess the fidelity to the intervention by supervising procedures.

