**Methods/design:**

Pregnant women (*n* = 150), who attend antenatal clinics at Westmead Hospital in New South Wales, Australia, have a keloid scar from a previous caesarean section, meet the inclusion criteria and sign the consent form, will be randomised to either the control or the intervention group. The control group will receive surgical excision of the keloid scar at the beginning of the procedure during skin incision. The baby will be delivered according to normal procedures, and routine wound closure will be performed in accordance with National Institute for Health and Care Excellence guidelines. The intervention group will receive surgical excision of the keloid scar after the delivery of the baby, and closure of the uterus layers, rectus sheath and the fat layer will be completed as explained above. Then, triamcinolone acetone will be injected sub-dermally at the time of wound closure. Two ampules of triamcinolone acetonide will be administered at a single dose; each ampule contains 10 mg/1 ml active medication. The surgeon will inject one ampule along the entire length of the upper edge of the skin incision and one ampule along the entire length of the lower edge of the skin incision, using a 25 G needle. After the procedure is completed, the surgeon will fill in the post-operation survey.

The participants will be followed up post-operation, daily on the ward and then at 6 weeks, 6 months and 12 months post-partum. Main outcomes are (1) keloid formation after caesarean section and (2) changes in the appearance and specification of the keloid scar after the intervention.

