Based on the cellular mechanism of keloid formation, one of the first-line options to treat keloid scars is corticosteroid injection into the affected area. The steroids have both direct anti-inflammatory and vasoconstrictive effects. Administration of corticosteroids results in the whitening of keloid scars, suggesting a decrease of blood flow in the scar due to vasoconstriction [7].

Another suggested treatment of keloid scars is surgical removal of the scar. However, since surgical removal of the keloid usually only provides temporary cosmetic relief and invariability followed by even more aggressive regrowth of scar tissue in 50–100% of cases, many clinicians perform surgical excision of the keloid scar followed by sub-dermal corticosteroid injections. This has been suggested to be effective for patients with small or single site lesions [9].

Some studies have used immediate wound edge corticosteroid injection after the excision in patients with hypertrophic scars and keloid scars, followed by regular injection of corticosteroid: usually a weekly injection for 2–5 weeks followed by monthly injections for 3–6 months [10]. This combination of surgical removal and corticosteroid injections has been shown to improve outcome. This dose of steroid is substantially more than the stat dose we plan to use in our study and requires multiple visits and repeated injections.

A thorough literature search has shown a lack of research on the surgical excision and injection of corticosteroid injection immediately after the excision of the existing caesarean section keloid scars. Therefore, in the proposed study, we aim to investigate the effect of corticosteroid (triamcinolone acetonide) injection immediately after surgical removal of old caesarean section keloid scars on the recurrence of the scars.

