### Composite primary objective

A primary objective is to determine if surgical excision and sub-dermal injection of triamcinolone acetonide at the time of subsequent caesarean section is effective in preventing or reducing the amount of keloid formation in patients with a previous history of keloid scar after caesarean section. We also aim to investigate whether the appearance and specification of the keloid scar changes after the intervention (type of response).

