### Randomisation

Through a parallel intervention assignment, the independent researcher will use a computer-Vgenerated random-numbers list to determine group allocation. The researcher will then place each allocation into sequentially numbered opaque envelopes. There will be permuted blocks of 10 with 1:1 allocation, containing 5 intervention and 5 control allocations in each block. This will help achieve balance across the two groups.

For those who are randomised to triamcinolone acetonide, the independent researcher will insert the medication inside the envelope and, after sealing it, will store the envelope in a locked cabinet inside the medication room in the birth unit. The surgeon who is rostered on the day of the caesarean section will be informed of the recruited participant and will be instructed on where to collect the concealed envelope. All participants will have their randomisation number indicated in the hospital electronic record at the time of study allocation. This is done to inform the researcher assessing the outcomes of the recruiting of the participant and the allocated number, but not the allocated intervention.

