Local infection was reported in an earlier study after the sub-dermal corticosteroid injection therapy [29]. However, this has not been reported in a more recent research in which they injected 40 mg/ml triamcinolone acetonide (0.1 ml) sub-dermally [30]. This risk has been suggested to increase after an overdose of the local injection of corticosteroid [29]. Since we aim to use a small dose of triamcinolone acetonide (10 mg/1 ml) along the entire length of each edge of the skin incision at the time of caesarean section, we expect this risk to be minimal. Nevertheless, we will carefully assess the participants in our study to ensure safety.

We noted the established use of triamcinolone acetonide suspension 10–40 mg/ml in the treatment of other surgical wounds, where it is injected sub-dermally depending on the site. This treatment will eventually flatten 50– 100% of keloids, with a 9–50% recurrence rate [10, 31]. The use of corticosteroid injection following keloid surgery reduces the recurrence rate to less than 50% [32]. Usually, two or three injections are given a month apart; however, therapy can continue for 6 months or longer [33].

New keloids are more responsive to therapy than older, established lesions. In theory, this injection will prevent any scar formation before treatment is started. If our study hypotheses are true, then steroid injection presents as a safe and sustainable treatment in the management of keloid scars. Our findings will be particularly useful for patients unable to undergo cosmetic surgery due to clinical or financial reasons and in under-resourced settings both within Australia and internationally. Since we do not have access to the plastic surgery data, we are unable to investigate the cost-effectiveness of the treatment. However, we hope that our findings will provide knowledge for further future research investigating the cost-effectiveness of sub-dermal triamcinolone acetonide for the treatment of caesarean section keloid scars.

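### The arms differ in when the keloid is excised as well as in triamcinolone, so a difference between them cannot be credited to the injection alone

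*Protocol article*

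**What the plan says.** Protocol article, Procedures, on the control arm: "The control group will receive surgical excision of the keloid scar at the beginning of the procedure during skin incision". On the intervention arm: "The intervention group will receive surgical excision of the keloid scar after the delivery of the baby". Uterus, sheath and fat are then closed in the same way as in controls, and two ampules of triamcinolone (10 mg in 1 ml each) are injected along the wound edges. Controls receive no injection, and no vehicle is described.

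The Methods/design part of the Abstract gives the same two timings ("The intervention group will receive surgical excision of the keloid scar after the delivery of the baby, and closure of the uterus layers" for the intervention arm), so this is not a slip in one place. The article gives no reason for the difference.

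On when the arm becomes known, Procedures says "The surgeon opens the envelope when the woman is ready for the caesarean section", which is before any excision. Randomisation adds: "For those who are randomised to triamcinolone acetonide, the independent researcher will insert the medication inside the envelope".

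On purpose, the Background says "we aim to investigate the effect of corticosteroid (triamcinolone acetonide) injection immediately after surgical removal". The primary objective is worded as a package: to "determine if surgical excision and sub-dermal injection of triamcinolone acetonide at the time of subsequent caesarean section is effective". The Discussion returns to the drug: "If our study hypotheses are true, then steroid injection presents as a safe and sustainable treatment in the management of keloid scars".

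**The concern.** Both arms have the keloid removed. If it were removed at the same step, the planned difference between arms would be the injection. As written, two things change together: when the scar is excised and whether triamcinolone is given. A difference in recurrence could come from either or both, and a null result could hide a drug effect offset by timing.

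At stake is the conclusion the authors want, that a single injection after excision reduces recurrence. Safety is affected too. The Data and safety monitoring section asks the committee to tell steroid harms apart from surgical complications, which is harder when the surgery also differs by arm.

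A secondary point is that the surgeon knows the arm while removing the scar, and the same surgeon later records whether removal was complete. The Blinding section accepts that the surgeon cannot be blinded to the intervention. But if excision were done at a common step, the arms would not need to diverge until after fat-layer closure, so excision could be done without knowledge of the arm.

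**Working it through.** **Inputs.** Sample size section: 75 per arm, 45% versus 70%, 80% power, two-sided 5%, 10% non-compliance. Randomisation section: 1:1 allocation. Procedures section: timing of excision and injection by arm.

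**1. The plan's own figure.** With mean proportion 0.575 and difference 0.25, the uncorrected size per arm is

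(1.960 × √(2 × 0.575 × 0.425) + 0.8416 × √(0.45 × 0.55 + 0.70 × 0.30))² / 0.25² = (1.3702 + 0.5693)² / 0.0625 = 60.2, so 61.

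With continuity correction: (60.19 / 4) × (1 + √(1 + 4 / (60.19 × 0.25)))² = 15.05 × 2.125² = 67.95, so 68. Then 68 × 1.10 = 74.8, so 75 per arm and 150 in total (68 / 0.90 gives 76 and 152). The stated 150 reproduces, and this point does not dispute its arithmetic.

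**2. Planned cells.**

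| | No triamcinolone | Triamcinolone |
|---|---|---|
| Excision at skin incision | 75 | 0 |
| Excision after delivery | 0 | 75 |

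**3. What the comparison estimates.** Write p(timing, drug) for the outcome probability. The arm difference is

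p(late, drug) − p(early, none) = [p(late, drug) − p(late, none)] + [p(late, none) − p(early, none)].

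The first bracket is the effect of the injection and the second the effect of timing. Both contain p(late, none), which no planned patient supplies. Splitting the other way needs p(early, drug), which is also unobserved.

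**4. Whether a model can help.** With an intercept, arm and late excision as columns, arm and timing have correlation 1 and the matrix has rank 2 for 3 coefficients. This restates step 3. The logistic regression in the Data analysis section, which adjusts for number of keloids and demographics, therefore cannot recover the drug effect. Women whose excision departed from plan would not be a randomised comparison.

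**5. Illustration only.** The documents give no timing effect, so the values below are assumed to show a range; they do not estimate bias. The control rate is 45%, with 75 per arm and no non-compliance.

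Example at 5 points in favour of late excision, with no drug effect (45% versus 50%):
- Null standard error: √(0.475 × 0.525 × 2 / 75) = 0.0815.
- Alternative standard error: √((0.45 × 0.55 + 0.50 × 0.50) / 75) = 0.0814.
- Rejection probability: Φ((0.05 − 1.960 × 0.0815) / 0.0814) + Φ((−0.05 − 1.960 × 0.0815) / 0.0814) = 0.089 + 0.005 = 0.094.

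The same formula gives the second column of the table. The third column is the power when timing works against the intervention arm and the true 25-point difference shrinks by that amount.

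| Assumed timing effect | Rejection rate, no drug effect | Power, 25 points less the timing effect |
|---|---|---|
| 0 | 5% | 88% |
| 2.5 points | 6% | 80% |
| 5 points | 9% | 70% |
| 10 points | 23% | 45% |

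A small timing effect would do little harm and a moderate one a good deal. The design gives no means of telling which applies.

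**The case against.** The strongest reply is that the trial tests a package. The article's title, the aim and conclusion in the Abstract, the hypothesis, the primary objective and three of the four secondary objectives all name excision together with injection. The injection-only reading rests mainly on one sentence in the Background and one in the Discussion. This is correct, and it is why the randomised comparison itself is not in doubt. It does not remove the problem: controls are excised too, and no objective names timing as part of the treatment, so package wording neither explains nor discloses the difference.

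Second, nothing in the documents suggests that timing within one operation affects recurrence up to 12 months. That stands as a limit on the size of the concern. It does not show that the effect is zero.

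Third, the article condenses a fuller protocol that may give a surgical reason. Late excision does bring removal closer to an injection given at closure. That could justify late excision in the intervention arm, but it does not explain why controls could not be excised at the same step.

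Fourth, surgeon awareness is disclosed, and training, supervision and a record of complete excision in both arms help with technique. This is fair. Those measures do not equalise timing, and the person completing the record knows the arm, but delaying the reveal is an improvement of secondary weight.

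**Conclusion.** The concern holds and should be fixed. By protocol, timing of excision coincides with triamcinolone in all 150 planned women, so the trial estimates late excision plus triamcinolone against early excision. That is a valid answer about two packages, but not about the injection alone, and no analysis can turn it into one.

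Confidence in the aliasing is high, because it follows directly from the text in two places. It assumes that the article states the timings as the full protocol does and that surgeons follow them. The practical size is unknown, since neither magnitude nor direction of a timing effect can be derived from the documents.

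**What to change.** Specify the same operative step for excision in both arms; which step is for the clinical team. Word the objective as triamcinolone added to excision versus excision alone. Without a vehicle injection the contrast remains triamcinolone injection versus no injection, and the text should say so.

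As a useful addition, reveal the allocation only after excision and fat-layer closure. Because only intervention envelopes contain medication, this also needs envelopes matched across arms or the drug stored separately, so that packaging does not disclose the arm.

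If a common step is not feasible, give the reason, state that two packages are compared, and revise the Background aim and the Discussion so that neither credits the injection alone.

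The cost is an amendment to the procedure text and surgeon training, plus packaging or drug storage if the reveal is delayed. Recruitment began in May 2019, so women treated before the change must be flagged. The sample size stays at 150 and no visits are added.

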### Follow-up

The follow-up period consists of 12 months face-to-face visits (Fig. 1). Post-operation, the patients will be visited daily on the ward for any signs of potential infectious local complications of the treatment and immediate side effects of the medication injection until the discharge home. The patients will then be visited in the women’s health clinic at the hospital for their 6th week post-partum check. The next follow-up times will be 6 months and 12 months post caesarean section. At each follow-up visit, the same assessment and scoring scales will be used to evaluate the changes to the keloid scar. Late side effects of the medication injection as well as symptoms of depression, anxiety and stress, and participants’ satisfaction will be assessed during follow-up visits at 6 weeks, 6 months and 12 months post-partum. The participants will also be asked if they would recommend such a procedure to another woman with a caesarean section keloid scar (yes/no) and if they would repeat the experience again in a future pregnancy (yes/no).

All measurements at baseline and follow-up visits will be performed by the same researcher, who will also make all efforts to ensure compliance with follow-up. As part of continuous clinical care, patients with any residue keloid scar with be given information on further treatment including referral to plastic surgeons if they are interested (Fig. 2).

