### Secondary objectives

Secondary objectives of the trial are to:Evaluate the effect of surgical excision and keloid scar treatment on symptoms of depression in women with keloid scarsDetermine whether surgical excision and sub-dermal injection of triamcinolone acetonide at the time of caesarean section changes the appearance (width, length, height) and specification (redness, hardness and elevation of the scar compared to the surrounding skin as well as discomfort including itching, pain and swelling) of the keloid scarAssess side effects of the surgical excision and sub-dermal injection of triamcinolone acetonide at the time of caesarean sectionInvestigate patients’ satisfaction with the treatment and their perception with the changes in their keloid scar after surgical excision and sub-dermal injection of triamcinolone acetonide at the time of caesarean section.

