### Secondary outcomes

The secondary outcomes are:Percentage of women with depression, anxiety and stressPatients’ satisfaction with the treatment and changes in their keloid scars.

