### Data analysis

Intention-to-treat analysis will be performed using SPSS Advanced Statistics version 24.0 (SPSS, Chicago, IL, USA). Descriptive statistics will be used to summarise the demographic data; binary outcomes will be summarised with a relative risk (RR) and 95% confidence intervals (CIs) and compared between the two groups using a χ^2^ test (or Fisher’s exact test where applicable). Comparison of the number of patients with keloid formations within groups and between the two groups will be done using a χ^2^ test. A *t* test will be used to assess continuous non-skewed variables; these will be presented as means with standard deviations. For skewed ordinal data, the Mann–Whitney *U* test will be used; these data will be presented as medians with interquartile ranges. Difference in the effect over the sub-groups will be assessed using logistic regression. Outcomes of interest will be number of patients with keloid formation, changes in the appearance and specification of the keloid scar, depression, anxiety, stress and patient’s satisfaction. Changes in the appearance and specification of the keloid scar after the intervention will be summarised into two groups (binary outcome: 0 = changed, 1 = not changed) and will be analysed using logistic regression adjusting for the number of keloids formed and demographic variables. A *p* < 0.05 will be considered statistically significant.

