### Harms

If there is a reasonable suspected causal relationship with the intervention, the study researcher who is blinded to the allocations will report to the data and safety monitoring committee, who will in turn report the adverse events to the ethics committee to guarantee the safety of the patients. We do not expect any risks for either group (control or intervention).

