## Discussion

Keloid formation often can be prevented or reduced if anticipated with immediate therapy. Once established, keloids are more difficult to treat, with a high recurrence rate regardless of treatment. Corticosteroids are a commonly used and effective treatment for established keloids on wounds in other area [16–18]. Corticosteroids suppress inflammation by inhibiting fibroblasts and mitosis while increasing vasoconstriction in the scar [19, 20]. Their effectiveness and side effects in subsequent caesarean section for those with established keloids has not been established. Yet caesarean section is easily the most common operation done, and keloid formation in these young women of childbearing age can be very distressing [3, 6, 21–23].

Other treatment modalities have also been used for keloid scars after caesarean section. Radiation therapy has been used with some clinical success [24, 25]. However, this modality of treatment requires multiple visits for radiation therapy during the post-natal period when more time is needed to care for the newborn. Our mode of treatment with a single administration of triamcinolone acetonide takes into consideration the need of the mother to have time to care for her newborn.

Common adverse effects of triamcinolone acetonide include atrophy, telangiectasia and hypopigmentation [26]. Steroids have been implicated as an aetiology in delayed wound healing. Although there is evidence in the literature that steroids delay wound healing, most studies are performed in vitro or use high systemic doses. Although wound disruptions have occurred in patients taking corticosteroids [26], treatment doses are generally below the level required for inhibition of wound healing in clinical practice. Acute, high-dose systemic corticosteroid use likely has no clinically significant effect on wound healing [27]. There is a retrospective evaluation study of post-operative intralesion steroid injections on wound healing [28]. Overall, there was not a statistically significant difference between the steroid groups and the non-steroid group. Therefore, one-time post-operative intralesion steroid injections were not found to delay wound healing [28].

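### Side effects are a stated secondary objective but no listed outcome, and a wound complication that starts after discharge and clears before 6 weeks is recorded only if the woman telephones

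*Protocol article*

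**What the plan says.** All references are to the protocol article.

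- **Secondary objectives** include assessing "side effects of the surgical excision and sub-dermal injection of triamcinolone acetonide at the time of caesarean" section.
- **Secondary outcomes** has two entries: the percentages with depression, anxiety or stress, and patients' "satisfaction with the treatment and changes in their keloid scars".
- **Data analysis** states: "Outcomes of interest will be number of patients with keloid formation, changes in the appearance and specification of the keloid scar, depression, anxiety, stress", and then adds satisfaction. The same section gives a general rule for binary outcomes: relative risk, 95% confidence interval, and a chi-squared or Fisher test.
- **Follow-up** provides daily ward visits for infectious local complications and immediate injection effects until discharge, then visits at 6 weeks, 6 months and 12 months. The harm item named for those three visits is the first part of "Late side effects of the medication injection as well as symptoms of depression, anxiety and stress". The keloid scales are repeated at each visit.
- **Data and safety monitoring** repeats that ward review ends at discharge. It gives women a number to ring about any problem with the scar, with hospital review if needed. It also sets up an independent committee whose tasks include separating steroid harms from surgical ones.
- **Harms** makes onward reporting depend on a suspected causal link, raised by a researcher blinded to allocation, and says "We do not expect any risks for either group (control or intervention").
- **Discussion** says "Common adverse effects of triamcinolone acetonide include atrophy, telangiectasia and hypopigmentation". It also mentions wound disruption and local infection, and largely discounts both at the planned exposure.

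**The concern.** An objective that matches no listed outcome has no stated comparison to answer it. The timing adds to this. The Discussion raises wound infection, wound disruption and delayed healing, and these can begin and end between discharge and 6 weeks. In that interval nothing is scheduled, and at 6 weeks the named harm item does not ask about it.

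The wording of that item is a second difficulty. A blinded assessor can see thinning or loss of pigment in any woman, but cannot say that it is an effect of an injection without knowing whether one was given.

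At stake is how a small number of recorded events would be read. The abstract anticipates a safe treatment, and the Discussion ties safety to the study hypotheses being true. Those hypotheses concern recurrence, satisfaction and depressive symptoms; none concerns harm. Few recorded complications could then be taken as evidence of safety when they partly reflect how complications were sought.

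**Working it through.** The plan states no figure for harms, so the check is mainly a comparison of sections.

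**1. Objective against outcomes.** The objective covers "side effects of the surgical excision and sub-dermal injection of triamcinolone acetonide". The two secondary outcomes are mood, and satisfaction with scar change. The outcomes of interest are keloid formation, scar change, depression, anxiety, stress and satisfaction. No infection, wound or skin-effect outcome appears in either place. The general rule for binary outcomes would suit one, but none is named for it to act on.

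**2. Schedule against the hazards named.**

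| Period | Scheduled harm check | Other route |
|---|---|---|
| Birth to discharge | Daily; infection and immediate injection effects | – |
| Discharge to 6 weeks | None | Woman telephones |
| 6 weeks, 6 months, 12 months | Late effects attributed to the injection | Keloid scales, photographs |

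If the stay is L days (not stated), the interval without a scheduled check is 6 × 7 − L = 42 − L days.

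**3. What the other items can show.** The scales grade redness, hardness, elevation and symptoms, and the scar is photographed. A wound still open or inflamed at 6 weeks may show up. An infection treated and healed by week 3 would leave little for these items to record.

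**4. Attribution.** The Blinding section masks both participants and the outcome assessor. Late effects of the injection, and the causal trigger in Harms, both ask for a judgement that depends on allocation. The committee's task of separating steroid from surgical harm needs the same events counted in the same way in both arms, and no section of the article defines those events.

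**5. Precision at 75 per arm.** The documents give no complication rates, so the following rests on assumptions. For rates p1 and p2, n = 75 per arm and two-sided 5%, with p̄ the mean of p1 and p2:

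power = Φ{[|p2 − p1| − 1.96·√(2p̄(1 − p̄)/n)] / √([p1(1 − p1) + p2(1 − p2)]/n)}

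Assume a true doubling of complications:

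- control rate 3%: about 14%
- control rate 5%: (0.05 − 1.96 × 0.0430)/0.0428 = −0.80, about 21%
- control rate 8%: about 32%
- control rate 10%: about 40%

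If half of the events were captured, the 5% case falls from about 21% to 12%, and the 10% case from about 40% to 21%. Over this range the harm comparison is one of estimation, not of testing, and incomplete capture weakens it further.

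**The case against.** The other side has good points.

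- *Follow-up is not confined to drug effects.* The same scar examination, symptom questions and photographs are used at each visit, and the symptom list is open-ended. This stands: a problem still present at 6 weeks may be seen. It does not cover one that has resolved.
- *There are safeguards between visits.* The telephone line is worded for any reaction or complication of the scar, without regard to arm, and an independent committee reviews all data. This also stands as partial cover. The line depends on the woman calling, and the committee can review only what has been recorded.
- *This is a condensed article.* The schedule figure is not shown, and event definitions and safety tables often sit in the full protocol or analysis plan. That excuses missing detail. It does not explain why an objective that the article states is absent from the outcomes that the article lists.
- *The Discussion plays down the risks.* It regards usual doses as too low to inhibit healing, cites a retrospective study that found no delay, expects minimal infection risk and promises careful assessment. So the conflict with the Harms section is narrow: a list of common adverse effects and a minimal risk on one side, no expected risk on the other.

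A reader might also infer that harms are to be assessed in the intervention arm only. The text does not support this. Follow-up does not restrict the item to one arm, and an assessor who does not know allocation would have to put it to every woman. The fault is in the label, not in one-sided collection.

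**Conclusion.** The point holds as a mismatch between the article's own sections. The side-effect objective has no named outcome. Wound complications that begin after discharge and resolve before 6 weeks are captured only passively. The late harm item asks for an attribution that blinding rules out. A difference between arms could therefore be under-recorded.

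The size of the loss cannot be derived from the documents, which give no length of stay, complication rate or rate of calling. The power figures above show only that 75 per arm leaves little information to lose, under assumed control rates of 3% to 10% and a doubling.

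A reader might go further and conclude that the trial can produce no count of complications by arm. That is not established: Data analysis does not call its list exhaustive, and its rule for binary outcomes could be applied to whatever is recorded. Nor do the documents show that an excess of wound complications is likely. The change should be made, but it does not bear on the primary comparison.

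**What to change.** 1. Under **Secondary outcomes** and **Data analysis**, add a secondary safety outcome: wound infection, wound disruption or delayed healing, skin atrophy, telangiectasia and hypopigmentation.
2. At the existing **6-week visit**, ask every woman in identical words that do not refer to the injection whether she has had any wound complication or wound treatment since discharge.
3. At **6 weeks, 6 months and 12 months**, replace the item on late injection effects with the presence or absence of each skin sign, recorded in all women.
4. Report each component by arm with relative risk and 95% confidence interval under the existing rule for binary outcomes, and present it as estimation.
5. Reconcile the statement in **Harms** that no risk is expected with the adverse effects and the minimal infection risk given in the **Discussion**.

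The cost is a few extra items on existing forms and one table, with no added visit. Recall over the weeks since discharge will carry some error, and intervals will be wide at 75 per arm; the report should say so.
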